## Abstract

**Background:**

The aim of the Perinatal Mental Health for Refugee Women (PMH-RW) Project is to investigate the impact of the war on perinatal mental health: anxiety, post-traumatic stress, depression, and birth trauma symptoms. It will also evaluate the factors that serve as protective elements for the development of these potential diagnoses (such as personality traits, social support, sociodemographic characteristics, and access to medical/mental health services).

**Method:**

An international observational cohort study with baseline data is being assessed in Ukraine (for internal refugees) and several European Countries (for external refugees). The study includes as participants both pregnant women and those who have recently given birth (with babies up to 1 year old). The assessment includes measures on depression (EPDS), anxiety (GAD-7), experiences during birth (City Birth Questionnaire), post-traumatic stress symptoms [Impact of events scale—revised (PTSD-R)], Personality (10-Item Personality Inventory-TIPI), and a questionnaire for socio-demographic data which also such social support.

**Conclusion:**

This study will provide needed information for determining the impact of the Ukrainian Crisis on perinatal mental health by studying potential risk and protective factors. The data collected will be used to inform policymakers with useful information that can be used in the development of plans to protect and promote the mental health of the perinatal refugees impacted by this event. Also, it is our hope that data collected from this study will serve to plant the seeds for further research regarding the impact of the crisis in Ukraine on the offspring and to analyze how these events are affecting further generations.

**Clinical Trial Registration:**

ClinicalTrials.gov, Identifier: NCT05654987.

## Introduction

United Nations Population Fund (UNFPA. Ukraine. Conflict compounds the vulnerabilites of women and girls, 2020), estimated that about 265,000 Ukrainian women were pregnant when the war broke out in February 2022. Eighty thousand women were expected to give birth in the subsequent 3 months in Ukraine or abroad (UNFPA. Ukraine. Conflict compounds the vulnerabilites of women and girls, 2020). The current migratory situation in Ukraine varies. The number of women fleeing the country, returning to Ukraine, and remaining in Ukraine even though the ongoing hostilities is difficult to estimate. However, it can be concluded that many Ukrainian women have experienced and will experience stress and/or possible adverse consequences (or trauma) related to the war and forced migration (Ancheva and Morozova, 2016; Zhabchenko et al., 2018; Romanenko, 2020).

To examine and suggest the most effective practices that may reduce the psychological effects of war refugee status on women, members of the “Research Innovation and Sustainable Pan-European Network in Peripartum Depression Disorder—Riseup-PPD” (Cost Action 18138), funded by the European Cooperation in Science and Technology (COST), established the “Perinatal Mental Health and War Refugees status” group.

Even in non-war conditions, the perinatal period (from pregnancy to the first year after the baby is born) is a vulnerable time *per se*. It is estimated that 1 in 5 women will develop a perinatal mental disorder, which implies that the onset and recurrence of mental health disorders during this period is very high (Andersen et al., 2012; Soto-Balbuena et al., 2018, 2021; Fawcett et al., 2019; Legazpi et al., 2022a,b). Depression, posttraumatic stress disorder (PTSD), and anxiety are shown on the literature as the most recurrent diagnoses (Chrzan-Dętkoś et al., 2022). The consequences of war and migration can be particularly damaging for mothers and babies. Studies have shown that the trauma of war or moving to a new area can have long-term negative effects on mental health, leading to an increased risk of depression and post-traumatic stress disorder (PTSD; Hoppen and Morina, 2019; Hoppen et al., 2021).

Mental health professionals who specialize in working with refugees have identified pregnant women and recent mothers as particularly vulnerable members of the migrant community because they are “in a precarious situation in a foreign country, when the sense of inner homelessness can easily develop, and the capacity for empathy and intuitive parenting can be weakened” (Utari-Witt, Walter, 2021, p. 58). For example, a study carried out in war-affected Syria indicated a high percentage (28.2%) of women is at high risk for postpartum depression (Roumieh et al., 2019).

It is also important to note that experiencing war can increase the chances of having a difficult pregnancy and delivery, as well as negative experiences related to childbirth (Fatusic et al., 2005; Arnetz et al., 2013). Along the same lines, exposure to armed conflict can lead to premature birth and babies with low birth weight (Fatusic et al., 2005; Davis and Sandman, 2010; Keasley et al., 2017). However, the likelihood of premature births, stillbirths, and miscarriages increases when there is direct exposure to conflict. For instance, the negative effects often stem from being exposed to a toxic environment with pollutants, radiation, exhaust fumes, or even water or food that has been contaminated in a war zone (Arnetz et al., 2013). Additionally, emerging research has found that women who fled from the Ukraine war experience significant changes in their status, including a loss of a previous lifestyle, daily contact with friends and relatives, financial losses, changes in perinatal health care associated with limited access to health care, and difficulties in finding a health professional (doctor or midwife) that meets all the medical needs (Chrzan-Dętkoś et al., 2022). Additionally, these women report having limited social support (lack of friends, relatives) and live in isolation as a result of being an immigrant (external refugee); research has found that lack of social support (perceived or actual) is a significant risk factor for developing several mental illnesses during the perinatal period (Marcos-Nájera et al., 2020, 2021).

Another risk factor for mental health is the individual adaptation to a new life in the host country. Heslehurst et al. (2018) reported daily difficulties faced by immigrants and asylum seekers in the host country: not knowing the language and being unfamiliar with the local lifestyle and health practices can create additional burdens and risks for mental and general health. Systematic reviews report that perinatal outcomes such as mental health, maternal mortality, preterm birth and congenital anomalies are predominantly more severe among migrant women (Falah-Hassani et al., 2015: Heslehurst et al., 2018). In a German study, 87.4% of the pre-and postpartum migrants were affected by medical complications or high-risk pregnancies (Kaufmann et al., 2022). However, these studies often do not distinguish among the different statuses of migrant (refugee vs. immigrant) populations, and host countries that may significantly differ regarding the organization of access to support and health care services. For example, an Australian study (Snow et al., 2021) showed elevated psychosocial risk factors among women of refugee background compared with Australia born-women, with the possible under-reporting of mental health problems and family violence. Research on healthcare for pre-, peri- and postpartum refugee women in high-income countries has shown that their access to health care is hampered by immigration experiences, insufficient health literacy, poor language skills, insufficient perception of health needs and use of health services, and legal restrictions (Haith-Cooper and Bradshaw, 2013; Rizkalla et al., 2020). These results raise questions regarding assessing psychosocial risk within different cultural groups and show the importance of the culture-sensitive approach to women with different cultural backgrounds. A systematic review and meta-analysis showed that the prevalence of current PTSD among migrants exposed to armed conflict is 31%, the current major depressive disorder is 25%, and the prevalence of generalized anxiety disorder is 14% (Mesa-Vieira et al., 2022). Migrating to a middle-income or low-income country was associated with an increased prevalence of generalized anxiety disorder—however, evidence is still scarce (Fellmeth et al., 2018).

Pre-migration experiences, migration and experiencing perinatal complications can profoundly impact the lives and mental health of both mother and child and have also been shown to have long-term effects on the mother–child relationship (Graignic-Philippe et al., 2014), day-to-day functioning as well as interpersonal relationships and past traumas (Fellmeth et al., 2018) Protecting and monitoring perinatal mental health in response to the war crisis in Ukraine is crucial (Sacchi, 2022). Focusing on helping this target group of refugees also gives the possibility to reduce the health costs associated with poor perinatal health, such as depression and prevent child development and intergenerational transmission of adversity and trauma. Determining factors that increase the likelihood of developing PPD, anxiety and PTSD in war affected population could help identify women at risk and improve efforts at prevention and early detection. In non-war and forced migration condition, personality traits such as neuroticism (Puyané et al., 2022), perfectionism (Gelabert et al., 2012), poor social support and a personal history of psychopathology (Robertson et al., 2004) are well established risk factors for perinatal mental health disorders—however, not much is known about their role in war affected population.

Generally, research indicates that many factors associated with perinatal depression are more context-specific and vary according to culture (Fellmeth et al., 2018). It is essential to carry out more thorough investigations to evaluate the psychological distress of women, as well as the potential risks and protective factors in varied contexts (internal vs. external refugee) that have emerged due to war, in order to lay a reliable foundation for comprehending the effect of war on women’s mental health during pregnancy.

As Chrzan-Dętkoś et al. (2022) has pointed out, more research should focus on different topics (e.g., risk and protective factors for the perinatal mental health status). The first necessary step should be to develop a comprehensive definition of psychological distress in this target group. Depression and anxiety are the most prevalent psychological diseases in the perinatal period, but PTSD is also an important disorder related to the impact of war and migration (Andersen et al., 2012; Hahn-Holbrook et al., 2017; Shorey et al., 2018; Fawcett et al., 2019). Conducting more research regarding the prevalence and prevention of mental health disorders during the perinatal period is essential. Not only it would benefit the implementation of prevention interventions to support mothers during pregnancy, but also it can have a very positive impact on the offspring (Caparros-Gonzalez et al., 2021). As Tuovinen et al. (2020) state maternal depression and anxiety are strongly related to an increase in inflammatory biomarkers in the mother during pregnancy. These increased numbers of biomarkers are associated with a higher risk of neurodevelopment delay in the offspring. Although fetal programming hypothesis is still under research and results show as inconsistent, there is a valuable truth that can be removed from it: that mothers and babies are interconnected, and that taking care of one implies taking care of the other.

The war in Ukraine brings new challenges to primary care and mental health services all over Europe. We focus on perinatal mental health, and to our knowledge, no previous studies have been conducted to study the impact of war in this field. Although for most European citizens, the date of the war outburst is 24 February 2022, the war in Ukraine, with all the consequences for the civil population, including pregnant and postpartum women, started in 2014. A study conducted in 2016 (Ancheva and Morozova, 2016) demonstrated PTSD frequency in 34.8% of pregnant women displaced internally. Another study showed an increased risk of reactive and personal anxiety, depressive manifestations, autonomic dysfunction, insomnia (Romanenko, 2020), and the risk of premature termination of pregnancy among war-affected population (Cox et al., 1987; Romanenko, 2020). Pregnant women who have been forced to relocate within their own country display a high amount of both reactive and personal anxiety. In pregnant women who were internally displaced, reactive anxiety was 3.3 times higher, and personal anxiety was 2.6 times higher than in pregnant women who were not internally displaced (Zhabchenko et al., 2018). However, to date, there are no publications on changes in the mental health of pregnant women and mothers of newborn children during the full-scale war in Ukraine. The research team intends to launch an international longitudinal study in order to address the lack of knowledge on the consequences of the war and the status of war refugees on maternal mental health during pregnancy. This article outlines the design of the study.

### Aim

The purpose of this upcoming research is to explore how the situation of war in Ukraine may be affecting perinatal mental health, such a anxiety, post-traumatic stress, depression, and birth trauma symptoms.

### Symptoms

Another objective is to evaluate possible risk and protective factors (including social and economic factors, personality traits, social support, and access to medical/mental health services). We are focusing on the two groups of women who were affected by war during pregnancy: those who left Ukraine and are now refugees in other European countries (known as external refugees) and those who chose to remain in Ukraine (in the same place of residence, considered as internal refugees).

The main goals are the following:To evaluate how perinatal mental health has been affected during the war, by observing the differences in (a) levels of depression, anxiety, post-traumatic stress disorder, and birth trauma; as well as in (b) clinical risk indices (proportion of women above the clinical cut-off point on a validated self-report scale)To research which risk and protective factors have a bearing on perinatal mental health during the war.To examine the links between pregnancy results and mental health of women in war-affected areas.To examine the experiences during the birth and delivery, specifically the potential traumatic events during this period.To assess the perinatal women’s needs concerning support and mental health services in Ukraine and in the host countries.

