## Methods

### Study design

This is an international observational cohort study. The rationale is to evaluate women’s perinatal mental health experiences throughout pregnancy and the first year after childbirth. The general study will extend from 01 December 2022 to 30 June 2023. This date can be changed depending on the situation of the war.

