### Participants

The research sample consists of females in the time around childbirth. To be included in the study at the beginning, participants must meet the following criteria:Being pregnant or a biological mother of an infant up to 12 months of age.Being 18 years or older.Being a war refugee from Ukraine (entrance to EU countries from 24 February 2022) or staying in Ukraine after/during the war.Consenting to take part in the study.

The exclusion criteria are:Not being currently pregnant or not being the biological mother of an infant up to 12 months of age.Younger than 18 years of age.Not consenting to take part in the study.

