**Independent/predictor**		
Social support	ACT-PNM	NA
Coping strategies	ACT-PNM	NA
Emotional impact	ACT-PNM	NA
War exposure	ACT-PNM	NA
Pregnancy outcome (birthweight, preterm birth, complications?)	ACT-PNM	NA
Health background/ earlier mental health, substance use,	ACT-PNM	NA
access to the perinatal health services	ACT-PNM	NA
Pregnancy outcome (birthweight, preterm birth, complications?)	ACT-PNM	NA

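### Eligibility admits mothers who gave birth before 24 February 2022, so the birth-experience and birth-trauma results would pool pre-invasion with wartime deliveries

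*Protocol article*

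**What the plan says.** All references are to the protocol article.

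- **Target population (Symptoms).** The stated focus is "the two groups of women who were affected by war during pregnancy": those now in other European countries and those who remained in Ukraine.
- **Perinatal criterion (Participants).** "Being pregnant or a biological mother of an infant up to 12 months of age". It sets no limit on the date of conception or birth.
- **War criterion (Participants).** "Being a war refugee from Ukraine (entrance to EU countries from 24 February 2022) or staying in Ukraine after/during the war". The date applies to entry into the EU. The group in Ukraine has no date, and neither arm of the criterion refers to the pregnancy.
- **Calendar (Study design).** "The general study will extend from 01 December 2022 to 30 June 2023". The article adds that the war may change this.
- **Start of the war (Introduction).** The article notes that most Europeans date the war from 24 February 2022, but says that "the war in Ukraine, with all the consequences for the civil population, including pregnant and postpartum women, started in 2014". The same section counts women pregnant at the February 2022 outbreak and names the full-scale war as the gap in the literature.
- **Goals and roles of variables (Symptoms, Table 1).** The first goal includes birth trauma levels during the war. The third is "To examine the links between pregnancy results and mental health of women in war-affected areas". The fourth concerns birth and delivery experiences. Table 1 lists "Pregnancy outcome (birthweight, preterm birth, complications" and war exposure as predictors, and birth PTSD (City BiTS) as an outcome.

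**The concern.** The stated focus is exposure to war during pregnancy, while the criteria fix only the infant's age and the mother's location or date of entry. A woman who delivered in December 2021 and crossed the border in March 2022 meets every criterion as an external refugee. Her whole pregnancy and her delivery came before the full-scale war.

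This matters most where the delivery itself is the object of study. The fourth goal describes birth and delivery, and City BiTS takes the birth as its index event. If pre-invasion deliveries are pooled with later ones, the results will be read as describing births in wartime when some do not. Among early enrolees these are also the mothers of the oldest infants, so timing of birth and time since birth cannot be separated for them.

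**Working it through.** The article gives no figure for this share, so there is nothing to reproduce. The check is calendar arithmetic.

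**Inputs from the article:** start 1 December 2022 and end 30 June 2023 (212 days); maximum infant age 12 months; 24 February 2022 as the date for external refugees; minimum sample 300.

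**Assumptions not in the article:** the study dates are the enrolment dates; births are spread evenly over the preceding year; accrual is even unless stated otherwise; 12 months is read as the same calendar date one year earlier.

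**Step 1, width of the window.** The earliest eligible birth on the first day is 1 December 2021. Days from then to 23 February 2022: 31 + 31 + 23 = 85.

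**Step 2, share by enrolment day.** With *i* days since 1 December 2022, the share of eligible postpartum women with a pre-invasion delivery is max(0, 85 − *i*)/365.

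| Enrolment date | Pre-invasion days | Share |
|---|---|---|
| 1 Dec 2022 | 85 | 23.3% |
| 1 Jan 2023 | 54 | 14.8% |
| 1 Feb 2023 | 23 | 6.3% |
| 24 Feb 2023 onward | 0 | 0% |

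The share is above zero on 85 of the 212 days (40%).

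**Step 3, averages.**

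- Whole window: 85 + 84 + … + 1 = 85 × 86/2 = 3,655; 3,655/(365 × 212) = 4.7%.
- All enrolment in December 2022: 85 + … + 55 = 31 × 70 = 2,170; 2,170/(365 × 31) = 19.2%.
- All enrolment from December to February (90 days): 3,655/(365 × 90) = 11.1%.

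**Step 4, number of women.** If all 300 were postpartum, 4.7% is about 14 women. If pregnant and postpartum women enrolled 9:12 (an assumption that follows the length of the two periods), the share of the whole sample is 0.047 × 12/21 = 2.7%, about 8 women. With all enrolment in December 2022 and all 300 postpartum, it is 0.192 × 300, about 58.

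**Step 5, which analyses are touched.**

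- *Birth experience (fourth goal):* affected directly, because the event described came before the invasion.
- *City BiTS (first goal):* the index event came before the invasion, but current symptoms may reflect later war experience. The score mixes the two.
- *Pregnancy outcome and mental health (third goal):* pregnancy outcome is a predictor and current mental health the response. Both can be measured correctly in these women; what changes is the population described.
- *Depression, anxiety, PTSD:* these women were postpartum during the war and belong in the analysis.

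**The case against.** The strongest reply is that this is loose wording in one sentence. Elsewhere (abstract, Study design, Participants) the population is pregnancy plus the first postpartum year, and these women fit it. That stands, and it is why they should not be excluded from the study.

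A second reply is that the article dates the war from 2014, so a birth in January 2022 was not outside the war. This is fair as to the wording. But a 2014 start would make nearly every recent pregnancy in Ukraine war-affected, and the phrase would then select nobody. The article's own rationale and its external group rest on the full-scale war. What follows is that the article uses two start dates and needs one definition.

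A third reply is that war exposure is already recorded in the study questionnaire, which is summarised and not shown. That also stands: one cannot conclude that the timing of birth goes uncollected. The article nevertheless sets a target that its criteria do not deliver.

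A reader might also infer that these women are misclassified as exposed, so that associations are pulled toward the null by 10 to 20%. The article does not support this. It plans no contrast of exposed with unexposed women on birth outcome, and it treats pregnancy outcome as a predictor. A share of that size would need recruitment concentrated in the first weeks. Online recruitment through social media makes that possible, but the article does not say it, and the Sample size section expects recruitment to be difficult.

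**Conclusion.** The mismatch is real and modest. The criteria admit deliveries up to 85 days before 24 February 2022, against a stated focus on war during pregnancy. Under even births and accrual this is about 5% of postpartum women. It could reach about 19% if all enrolment fell in December 2022, and it is zero for anyone enrolled from 24 February 2023. A later start would shrink or remove it.

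The consequence is a mixture of pre-invasion and wartime deliveries in the birth-experience and birth-trauma results, and a changed meaning for the pregnancy-outcome analysis. No amount of attenuation can be derived from the article. The current-symptom analyses are sound on this point.

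**What to change.** 1. Derive a flag for delivery before versus on or after 24 February 2022 from the infant's birth month. February 2022 straddles the cut-off, so births in that month also need the day or a direct yes/no question.
2. Restrict or stratify the birth-experience, City BiTS and pregnancy-outcome analyses by the flag. Under even accrual the pre-invasion group (about 14 women at most in 300) is too small for useful estimates of its own, so restriction with the pooled result alongside is the practical form. Stratification becomes worthwhile if early recruitment makes the group larger.
3. Keep all women in the depression, anxiety and PTSD analyses.
4. Use one definition of war exposure in the Introduction, the Symptoms section and the Participants criteria, including a date for women who stayed in Ukraine. Reword the stated focus if the wider postpartum population is intended.

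The cost is one derived variable, at most one added question, and a few sentences. The birth-related analyses lose about 5% of postpartum women under even accrual, and more if recruitment is early.

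### The internal-refugee group is defined as women who did not move, so eligible women displaced within Ukraine either fit no group or are merged with women who stayed put

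*Protocol article*

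**What the plan says.** Under Symptoms in the Introduction, the article announces two groups: "We are focusing on the two groups of women who were affected by war during pregnancy". One is "those who left Ukraine and are now refugees in other European countries (known as external refugees". The other is "those who chose to remain in Ukraine (in the same place of residence, considered as internal refugees".

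The eligibility criterion on location, in the Participants section, is broader: "Being a war refugee from Ukraine (entrance to EU countries from 24 February 2022) or staying in Ukraine after/during the war". It carries no same-residence condition. The exclusion criteria cover perinatal status, age and consent only, and displacement is not among them.

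The abstract's Method paragraph is broader still in its labelling: "baseline data is being assessed in Ukraine (for internal refugees) and several European Countries (for external refugees".

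The Introduction does separate displaced from non-displaced pregnant women inside Ukraine. It reports that in the displaced "reactive anxiety was 3.3 times higher, and personal anxiety was 2.6 times higher than in pregnant women who were not internally displaced".

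**The concern.** In the article's own Introduction, internal displacement means having had to move within the country. The group definition then gives the label *internal refugees* to women who stayed where they were. Women who moved within Ukraine are eligible, yet no section says which group they belong to.

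Two things are at stake. The first is interpretation: results reported to policymakers for internal refugees would describe either women who were never displaced or a mixture of unknown composition. The second is the comparison with women abroad. The Introduction names internal versus external as the contexts in which distress, risk factors and protective factors should be studied, and the Symptoms section builds its two groups on that line. Recruitment is open and online with no quota by displacement, so if the Ukrainian women are pooled, the mix is set by who responds.

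**Working it through.** The point is one of definition, so the main check sets the sections side by side. The plan gives no figure of its own to reproduce here.

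**Step 1: where each kind of woman falls.**

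| Situation | Eligible (Participants) | Group under Symptoms | Group under the abstract |
|---|---|---|---|
| Abroad in Europe | yes | external | external |
| In Ukraine, same residence | yes | internal | internal |
| In Ukraine, displaced | yes | none | internal |

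The third row is the gap. Under the definition read literally, these women drop out of both groups. Under the abstract's wording, they are combined with the second row.

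**Step 2: does the merge matter on the article's own evidence?** The Introduction cites reactive anxiety 3.3 times and personal anxiety 2.6 times higher in displaced than in non-displaced pregnant women. Anxiety, measured by the GAD-7, is one of the study's outcomes (Table 1).

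**Step 3: illustration of the size, for PTSD.** Inputs:
- displaced within Ukraine: 34.8% (study of pregnant women cited in the Introduction);
- abroad: 31% (meta-analysis of conflict-exposed migrants cited in the Introduction, used as a stand-in);
- non-displaced: 15%, range 10–20%. This is an assumption, as the article gives no figure.

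Prevalence in the merged group with displaced share *s* is *s* × 34.8 + (1 − *s*) × non-displaced rate.

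- *s* = 20%: 0.2 × 34.8 + 0.8 × 15 = 6.96 + 12.00 = 19.0% (15.0% to 23.0% over the assumed range).
- *s* = 50%: 17.4 + 7.5 = 24.9% (22.4% to 27.4%).
- *s* = 80%: 27.84 + 3.00 = 30.8% (29.8% to 31.8%).

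The difference, abroad minus merged group, at the assumed 15%:
- no displaced women: 31 − 15 = 16 points;
- half displaced: 31 − 24.9 = 6.1 points;
- all displaced: 31 − 34.8 = −3.8 points.

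The share at which the difference is zero is (31 − 15) / (34.8 − 15) = 16 / 19.8 = 81%. It is 21 / 24.8 = 85% if the non-displaced rate is 10%, and 11 / 14.8 = 74% if it is 20%.

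**Step 4: precision cost of splitting.** The 95% half-width for a difference at 30% prevalence in both groups is 1.96 × √(2 × 0.3 × 0.7 / n). Take the stated minimum of 300 women and assume equal groups:
- two groups of 150: 1.96 × √0.0028 = 10.4 points;
- three groups of 100: 1.96 × √0.0042 = 12.7 points.

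**The case against.** The strongest reply is that this is a wording fault with a limited consequence. Much of that stands.

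- **No formal internal-versus-external test is specified.** The first goal speaks of differences without naming groups, the Data analysis section compares outcomes across unspecified categorical variables, and Table 1 does not list refugee group as a predictor. A reader might infer that this is the study's only group contrast, or that a prespecified test is invalid. The article supports neither.
- **No section commits to pooling.** The abstract says where women are assessed. The study questionnaire records current residence, location after the outbreak and changes since the war began, so displaced women may be identifiable. Deriving group variables is often left to an analysis plan. That would excuse silence, but the article states a definition, and the definition conflicts with its eligibility criteria.
- **The prevalence inputs are not comparable.** The 15% is assumed, the 31% is not specific to perinatal Ukrainian women, and the 34.8% comes from a 2016 study. The anxiety ratios predate the full-scale war, in which women who stayed put also face missiles and power loss. The computed gaps are not the true contrasts.
- **A comparison by location has its own use.** The fifth goal asks about needs in Ukraine and in host countries. All women in Ukraine against all women abroad is coherent for that purpose.
- **Returnees.** A reader might infer that the criteria admit women who left and came back, since the Introduction mentions them. The criterion speaks only of staying in Ukraine, so this is unclear.

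**Conclusion.** The inconsistency is real and rests on the text alone: the group definition is narrower than the eligibility criterion and the abstract, and no rule places women displaced within Ukraine. The consequence is an ambiguous exposure group, misleading labelling and possible dilution of the comparison with women abroad.

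The size is illustrative only. With the assumed 15% in non-displaced women, the merged group's PTSD prevalence runs from about 19% to about 31% as the displaced share goes from 20% to 80%. A reader might infer that the sign of the contrast is readily at the mercy of the mix. The figures do not show that: against an assumed 31% abroad, it changes only above about 81% displaced (74% to 85% over the assumed range).

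**What to change.** Reconcile the Symptoms section with Participants and the abstract by defining three mutually exclusive groups:

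1. abroad;
2. in Ukraine and displaced;
3. in Ukraine at the same residence.

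State the reference date for displacement. The Introduction dates the war from 2014, so a date of 24 February 2022 alone would class women displaced earlier as non-displaced; say how they are handled. Add a rule for any returnees.

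Derive the groups from the residence and location items of the study questionnaire (ACT-PNM), after confirming that they capture prior residence, which its description does not explicitly list. Report the two Ukrainian strata separately. A pooled comparison of Ukraine with abroad may be kept for the fifth goal. Do not label non-displaced women refugees.

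The cost is wording, one derived variable and, if prior residence is not captured, an added item. Intervals widen to about 13 instead of 10 points of half-width with three equal groups of 100, and further if few displaced women respond.
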